### Outcomes

2.4

For the evaluation of NGS-performance (sensitivity, specificity, positive predictive value, negative predictive value), results of the NGS-based approach for each sample will be compared with those obtained using conventional microbiology methods for the same sample. Moreover, interobserver agreement will be assessed by the calculation of Cohens Kappa.

The clinical value of the NGS-based approach will be estimated by a panel of 3 independent clinical specialists not associated with the study site, retrospectively identifying potential changes in patients’ management based on NGS results. Therefore, the panel will be provided with clinical case summaries, NGS results, and standard-of-care results from all samples tested. Results of microbiological routine diagnostics in specimens different from blood [e.g., body fluid, tissue, bronchoalveolar lavage fluid (BALF), endotracheal aspirate] will be included when they have been obtained within a timeframe of ≤72 hours prior or after the timepoints for NGS-based measurements. To identify potential changes in antimicrobial management that may have occurred if the results from the NGS technology had been available for clinical use, the panel will be provided with a special questionnaire.

Secondary subgroup analyses will focus on the clinical value especially for patients suffering from a failure of empiric treatment within the first 3 days after onset [as assessed by death of the patient or a lack of improvement of the patient's clinical condition (in terms of an inadequate decrease of SOFA-score) or persistent high procalcitonin levels].

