### Statistical methods

2.12

For the evaluation of NGS-performance, results obtained with the NGS technology for each sample will be compared with those obtained using conventional microbiology methods for the same sample. Agreement and concordance will be assessed using a McNemar test and Cohen κ. All percentages and confidence intervals (CIs) for proportions will be calculated using the exact method and are rounded to the nearest percentage. Direct comparison of positive and negative results will be conducted with organism identification for each method (conventional microbiology vs NGS). Coagulase-negative Staphylococcus, xanthomonas, and other common skin contaminants will be annotated as “potential contaminants” for both methods and will be excluded from the overall analysis. Discrepant results between the NGS and culture-based techniques cannot be directly confirmed by an independent method. Two approaches will be used to resolve such discrepancies. In a subset of patients, multiple samples will be collected per standard-of-care. This includes 2 independent fresh venipunctures (left arm vs right arm) or 1 venipuncture and 1 sample collected from an indwelling line. Paired analysis of NGS testing results between these independently collected samples will be conducted to indicate the likelihood of true infection. In addition, independent clinical adjudication (described below) will be performed using all the clinical data collected as part of the study, including standard-of-care microbiology results and NGS results.

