The clinical value of the NGS-based approach will be estimated by a panel of 3 independent clinical specialists not associated with the study site by the use of a special questionnaire as described above. Analyses of the reviewers’ independent responses will be performed using a majority rule such that 2 of 3 responses for a given patient determine the outcome for that patient. Afterwards, special subgroup analyses (χ^2^ test for categorical data and further methods of variance analysis for continuous data) will focus on the clinical value especially for patients suffering from a failure of empiric treatment within the first 3 days after onset [as assessed by death of the patient or lack of improvement of the patient's clinical condition (in terms of an inadequate decrease of SOFA-score) or persistent high procalcitonin levels]. In addition, graphs are presented where possible. All statistical tests will be performed using SAS (SAS Institute, Cary, NC). A *P* value of less than .05 will be considered statistically significant.

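### NGS/culture discrepancies are resolved with the help of NGS itself, so any accuracy figure computed after resolution can rise or stay level but cannot fall

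*Protocol article*

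**What the plan says.** Section 2.4 (Outcomes) defines performance against conventional microbiology on the same sample: "For the evaluation of NGS-performance (sensitivity, specificity, positive predictive value, negative predictive value), results of the NGS-based approach for each sample will be compared". Section 2.12 (Statistical methods) repeats that comparison and adds: "Agreement and concordance will be assessed using a McNemar test and Cohen κ".

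Section 2.12 then turns to disagreements. It concedes: "Discrepant results between the NGS and culture-based techniques cannot be directly confirmed by an independent method". It continues: "Two approaches will be used to resolve such discrepancies".

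- Route 1 applies to a subset of patients with two separately collected samples: "Paired analysis of NGS testing results between these independently collected samples will be conducted to indicate the likelihood of true infection".
- Route 2 is independent clinical adjudication, which "will be performed using all the clinical data collected as part of the study, including standard-of-care microbiology results and NGS results".

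The adjudication is announced as described below. The only body described after that is the three-member specialist panel, whose stated task is to identify potential changes in management, with the rule that "2 of 3 responses for a given patient determine the outcome for that patient". Section 2.4 confirms what that panel sees: "the panel will be provided with clinical case summaries, NGS results, and standard-of-care results from all samples tested".

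The article describes no step in which the adjudicators judge infection without the NGS result. It also describes no review of true infection where NGS and culture agree.

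**The concern.** Section 1.3 makes the performance of NGS against culture-based diagnostics the primary objective. Where the two disagree, the plan lets NGS take part in deciding which was right. Two biases combine.

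- **Incorporation.** The adjudicators know the NGS result when they judge whether the organism was real. Paired NGS is likewise read as a sign of true infection, although both samples pass through the same laboratory, library kit, classification pipeline and SIQ model. Errors that NGS makes systematically can recur in both draws, so agreement between the draws shows repeatability rather than truth.
- **Discrepant-only review.** A ruling for NGS moves a result from a discordant to a concordant cell. A ruling against NGS leaves the table as it was. Errors shared by both methods are never opened.

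At stake is whether a resolved accuracy figure means anything. If it improves whenever the panel sides with NGS, and cannot worsen, it does not answer the study's question. The bias does not shrink with 500 patients, and a panel member who has seen the NGS result cannot afterwards give a blind judgement.

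**Working it through.** The article gives no accuracy figure to reproduce. The approximate 500 patients in section 2.8 are expressly not a power calculation and do not enter the argument.

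**Notation.** a = both positive; b = NGS-positive/culture-negative; c = NGS-negative/culture-positive; d = both negative. Let x results in b and y results in c be ruled for NGS. Then:

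- sensitivity = (a + x) / (a + x + c − y)
- specificity = (d + y) / (b − x + d + y)
- PPV = (a + x) / (a + b)
- NPV = (d + y) / (c + d)

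**Direction.** None of the four decreases in x or y. PPV moves only with x and NPV only with y. As a check, all tables with cells from 1 to 15 were enumerated with each of the two one-result moves: 15⁴ × 2 = 101,250 moves. Sensitivity, specificity, PPV, NPV, overall agreement and kappa fell in none of them.

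**Size, uninformative test.** All inputs are assumptions: NGS independent of culture, NGS positive in 50%, culture positive in 33%. The 33% is taken from an ambiguous sentence in the Discussion and serves only as an illustration; the 50% has no source. This gives a = 0.165, b = 0.335, c = 0.165, d = 0.335.

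| Ruled for NGS | Sensitivity | Specificity | PPV | NPV |
|---|---|---|---|---|
| none (raw) | 0.165/0.33 = 50% | 0.335/0.67 = 50% | 0.165/0.5 = 33% | 0.335/0.5 = 67% |
| 25% of b | 0.24875/0.41375 = 60% | 0.335/0.58625 = 57% | 0.24875/0.5 = 50% | 67% |
| 50% of b | 0.3325/0.4975 = 67% | 0.335/0.5025 = 67% | 0.3325/0.5 = 67% | 67% |
| 25% of b and c | 0.24875/0.3725 = 67% | 0.37625/0.6275 = 60% | 50% | 0.37625/0.5 = 75% |
| 50% of b and c | 0.3325/0.415 = 80% | 0.4175/0.585 = 71% | 67% | 0.4175/0.5 = 84% |

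**What full review changes.** Assume 500 results, 165 culture-positive, and a useful test: a/b/c/d = 132/100/33/235, so raw sensitivity is 132/165 = 80.0% and raw specificity 235/335 = 70.1%.

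- Discrepant-only, 50 of b ruled infected: sensitivity 182/215 = 84.7%, specificity 235/285 = 82.5%.
- The same, with 24 of the double negatives also judged infected: 182/239 = 76.2% and 211/261 = 80.8%.
- The same, with 47 of the double negatives judged infected: 182/262 = 69.5% and 188/238 = 79.0%.

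Once concordant results are reviewed too, sensitivity can fall below its raw value. Blinding alone would remove incorporation but leave the one-way movement, so both changes are needed.

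**The case against.** The case on the other side has six parts.

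1. **The accuracy result may be the raw one.** Sections 2.4 and 2.12 define it against culture, and nowhere is it said that resolved results replace culture in the table. This stands. A reader might infer that the headline figures will be the resolved ones; the article does not support that.
2. **Culture is an imperfect reference.** Section 1.1 describes false negatives under empiric antibiotics and false positives from contamination. A ruling for NGS may therefore be correct. This stands. A reader might infer that resolved figures must exceed true accuracy; what is shown is only that they cannot fall below the culture comparison.
3. **The panel receives all samples,** so it might judge infection in concordant cases as well. The questionnaire is not shown. But its described purpose is management changes, and section 2.12 ties resolution to discrepancies. If concordant results were judged too, the one-way movement would end.
4. **The larger illustrated gains need the panel to overturn positive cultures,** although skin contaminants, an obvious reason for doing so, are already excluded. This stands as a limit on size. At 50% siding, the whole NPV gain and 13 of the 30 points of sensitivity gain come from that assumption.
5. **Paired draws have value.** They can expose draw-specific contamination. Blanks, a library control, exclusion of Xanthomonas and the SIQ score also reduce systematic error (sections 2.5.2 to 2.5.4). This is fair, and the text does not say outright that paired draws reclassify results. It does list them as a way to resolve discrepancies, and these controls do not turn a second NGS result into a reference standard.
6. **The study is an exploratory pilot, and details may sit elsewhere.** Exploratory status explains the lack of power, not a circular reference. The point concerns a method that the article states, not a detail it leaves out.

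**Conclusion.** The concern holds for any accuracy figure computed after the described resolution. Such a figure cannot fall below the raw culture comparison, whatever the test is worth. Under the stated assumptions, a test unrelated to culture moves from 50% sensitivity and 50% specificity to between 60/57% and 80/71%, depending on how often, and in which discordant cells, the panel sides with NGS. These numbers illustrate the mechanism and do not forecast this study's results.

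The direction rests on one reading of section 2.12: that only discrepancies are resolved. The raw same-sample comparison is not affected. Whether resolved figures replace it or stand beside it is left open, and that should be settled before the panel starts.

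**What to change.** In section 2.12:

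- State that the raw same-sample comparison with conventional microbiology is the primary accuracy result.
- Have the existing three-member panel first classify every patient, concordant and discordant, as to infection and causative organism, using clinical data and all standard-of-care results but not NGS. Lock that answer, and only then disclose NGS for the management questionnaire.
- Base any adjudicated accuracy on the locked classification.
- Report the paired-draw NGS comparison as repeatability, and do not use it to reclassify results.
- Label any NGS-informed resolution as descriptive.

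The cost is NGS-free case files and staged release to three reviewers for about 500 patients, which is more than one extra questionnaire page but uses a panel that already receives all samples. Adjudicated figures will probably be less favourable, and some organisms found only by NGS will stay unconfirmed.

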### Data monitoring

2.13

If necessary, monitoring will be done by personal visits from a clinical monitor of the Department of Anesthesiology, Heidelberg University Hospital. The monitor will review the entries into the eCRFs on the basis of source documents. The investigator must allow the monitor to verify all essential documents and must provide support at all times to the monitor. By frequent communications (letters, telephone, fax), the site monitor will ensure that the trial is conducted according to the protocol and regulatory requirements.

### Harms

2.14

Due to the noninterventional character of *Next GeneSiS*, study-related adverse events (AEs) are restricted to complications of study-related blood draws (local lesions at puncture site or volume of blood draws). Such minor AEs are recorded in the eCRF. Serious AEs (SAEs) resulting in death, a life-threatening state, a prolongation of existing hospitalization, a persistent or significant disability or incapacity due to study participation are not expected.

### Auditing

2.15

Regular audits by the sponsor are not intended. For the purpose of on-site inspection or audit, the competent authorities may require access to all source documents, CRF, and other trial-related records. The investigator must ensure availability of these documents and support the work at any time.

### Ethics

2.16

Described procedures are meant to ensure that all parties involved abide by the principles of Good Clinical Practice (GCP)^[21,22]^ and those stipulated in the Declaration of Helsinki.^[23]^ The conducting takes place in accordance with local statutory and implementing provisions.

### Research ethics approval

2.17

Before the beginning of the clinical trial, the study protocol, the patient information and informed consent, and all other required documents will be submitted to the competent ethical review committees of all participating centers. A first positive ethical vote has been given by the Ethics Committee of the Medical Faculty of Heidelberg, Trial Code No. S-084/2017.

### Protocol amendments

2.18

Changes to the protocol are made in writing and require the approval of all signatories of the protocol. Subsequent amendments also require a positive assessment from the competent ethics committee.

### Consent or assent

2.19

The members of the study group must inform eligible patients, both orally and in writing in an intelligible form about nature, significance, and implications. Before participants can be enrolled in *Next GeneSiS*, they must consent to participation in writing. For potential trial participants who are incapable, there is another procedure.

If a legal guardian already exists, they are duly informed in accordance with the regulations and subsequently consent to participation in writing. If no legal guardian exists, participants are enrolled in the clinical trial after a near family member has been informed about nature, significance, and implications and has agreed to participation in the study mindful of the interest of the patient concerned (also by telephone). In summary proceedings, the designation of a legal guardian is begun at the district court. If no near family member is available, participants are enrolled after a guardianship judge has been informed about nature, significance, and has agreed to participation in the study mindful of the interest of the patient concerned (also by telephone). A near family member is appointed legal guardian earliest possible; they are duly informed in accordance with the regulations and subsequently consent to participation in writing (delayed consent). In any case, informed consent of study participants is sought retrospectively once they are capable of giving consent again.

### Confidentiality

2.20

Data collected are handled in accordance with the provisions of the Federal Data Protection Act (BDSG).^[24]^ During the clinical trial, participants are solely identified by a distinct reference number. For storage on a computer, the provisions of the BDSG^[24]^ are abided by. Data are handled with strict confidentiality. For protection of these data, organizational measures are taken to prevent disclosure to unauthorized third parties. The relevant rules of the country-specific data legislation are complied with.

### Justification for enrolment of participants not capable of giving consent

3.1

Bloodstream infections remain one of the major challenges in ICUs, leading to sepsis or even septic shock in many cases. Due to the lack of timely diagnostic approaches with sufficient sensitivity, mortality rates of sepsis are still unacceptably high. However, a prompt diagnosis of the causative microorganism is critical to significantly improve outcome of bloodstream infections. Although various targeted molecular tests for blood samples are available, time-consuming blood culture-based approaches still represent the standard of care for the identification of bacteria. With regard to these alarming figures, the current clinical trial (*Next GeneSiS*) is designed to investigate a new diagnostic approach, namely, NGS. The majority of the patients affected are sedated and given artificial ventilation. Even before sedated, affected patients sometimes need to be regarded incapable of giving consent due to the underlying severe infection, inflammatory response, and severe pain. Therefore, in these cases, informed consent to participate in *Next GeneSiS* needs to be given by a legal guardian until the affected patient is capable of consent. Nevertheless, especially, these critically ill patients need to be enrolled in *Next GeneSiS,* in order to assess the diagnostic value of the above-described NGS-based approach for the early detection of the causative microorganism in sepsis. This might help to improve outcome of patients suffering from sepsis due to an early optimization of the anti-infective treatment regime. This might especially be true for patients, where classic microbiological or molecular diagnostic approaches fail.
